**Fig. 1 Fig1:**
[figure not shown]
The schedule of enrolment, interventions and assessments

### Sample size

Some 2445 children are enrolled in fourth grade at public elementary schools in the Sukhbaatar district of Ulaanbaatar, Mongolia. 2337 children are enrolled in the ten schools that participate in this study. All the eligible children will be recruited.

This study is a longitudinal cluster randomized trial which has three-level cluster units: the school, individual, and measurement time point. Additionally, the number of students at each school differs. To calculate the statistical power, we implemented a simulation study extending the method of a previous study to adjust for unbalanced data. [40] We assumed the standardized difference of the primary outcome to be equal to 0.2, and the dropout rate to be equal to 5%. Since the statistical power of the longitudinal cluster randomized trial depends on the correlation between measurement time points for the same individual, we assumed values of 0.4, 0.5 or 0.6. Bonferroni correction was used to adjust for the multiplicity of statistical testing calculated for each site (Urban/*ger*/mixed residential). Table 1 shows the statistical power and alpha error for each site. We also simulated the disjunctive alpha error and power. In all assumption settings, the disjunctive alpha error is kept nearly equal to 0.05, and the statistical power of the urban site exceeds 0.8. Additionally, under conditions in which the correlation equals 0.6, the statistical power exceeds 0.8 for both sites. The simulation was done 5000 times using the mixed procedure with SAS Software 9.4 (SAS Inc., Cary, NC, USA).

**Table 1 Tab1:** Simulation results of statistical power

Correlation	Disjunctive: 5000 simulations Standardized difference = 0.2					
	Alpha error			Power		
	Total	Urban	*Ger* or mixed residential	Total	Urban	*Ger* or mixed residential
0.4	0.050	0.027	0.024	0.957	0.871	0.642
0.5	0.047	0.023	0.024	0.977	0.920	0.719
0.6	0.047	0.023	0.024	0.992	0.967	0.814

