As studies of children in the developed world have shown, physical activity deficits among children not only result in increased obesity and poorer athletic ability but may also have adverse effects on academic achievement and brain function. Similar trends are now being seen among children in emerging nations. Mongolia is one of these emerging nations now facing an epidemiological transition from infectious diseases to non-communicable and lifestyle-related health issues. In Mongolia, the physical activity deficit among children has become a serious problem in recent years especially in Ulaanbaatar, the capital city, where the shortage of outdoor play spaces caused by rapid urbanization, the spread of television and video games, and severe winter weather, have reduced the physical activity levels of children. In Ulaanbaatar, the average temperature is below freezing for more than five months per year. This fact has contributed greatly to increasing child obesity. In Mongolia, previous studies showed that the rate of overweight and obesity was 10.6 and 1.5%, respectively, among children aged 12–17. [29] Physical inactivity and obesity cause childhood health problems including diabetes mellitus, hypertension, hyperlipidemia, etc. Moreover, the adverse effects of exercise deficits are thought to have non-physical consequences including poor academic achievement and cognitive development. These health problems are common to middle-income earners worldwide, including those in developing countries like Mongolia.

The primary objective of our study is to investigate the effectiveness of exercise intervention on academic achievement among children using a large cluster RCT. The secondary objective is to investigate the effectiveness of exercise intervention on reducing the prevalence of obesity and overweight and on improving physical fitness performance, lifestyle, mental health, and cognitive function. The executive function was chosen as the target cognitive function based on the hypothesis that this function can best predict academic achievement.

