### Allocation

We will perform stratified block randomization to allocate ten schools into the intervention and control arms. These schools will be stratified into the urban area group (6 schools) and the *ger* or mixed residential area group (4 schools) according to the location of the school. To ensure a balance between the two study arms, we will order the schools by the number of fourth grade students to form blocks for randomization in each residential group. Within the blocks, the schools will be randomly allocated to the intervention or control arm. To allocate the schools, arbitrary numbers given by the representative of each school will be used. The arbitrary numbers will be processed by a program on R statistical software, version 3.4.3 (The R foundation for statistical computing platform) which is developed by a researcher. Each school will be randomly allocated to intervention or control group based on the output of the R program.

The allocation will be conducted and announced to the representative of each school at a kickoff meeting.

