#### Subgroup analysis

The effect of the intervention will be further analyzed using four subgroup analyses. The first subgroup analysis will focus on the location of the schools (urban and non-urban areas), the second on gender, and the third on baseline physical fitness performance using the median score on a 20m shuttle run. The fourth subgroup analysis will focus on baseline academic achievement using the total score on the national year-end examination in May 2017 and the median score. The fifth subgroup analysis will be done after excluding participants whose correct rate on the Flanker test is below 80% at either the baseline or endline surveys.

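### Table 1's power and alpha hold only if schools hardly differ in their change over time, an assumption the primary model shares and the text does not state

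*Protocol article*

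**What the plan says.** The Sample size section describes a longitudinal cluster trial with "three-level cluster units: the school, individual, and measurement time point". Its numerical inputs are these:

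- "We assumed the standardized difference of the primary outcome to be equal to 0.2, and the dropout rate to be equal to 5" percent.
- For the correlation between a child's two scores, "we assumed values of 0.4, 0.5 or 0.6".
- For the sample, "2337 children are enrolled in the ten schools that participate in this study".

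No school-level variance of change is given. From Table 1 the section concludes: "In all assumption settings, the disjunctive alpha error is kept nearly equal to 0.05, and the statistical power of the urban site exceeds 0.8". It also says that power passes 0.8 in both sites at correlation 0.6.

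The Allocation section randomises schools, not children: "These schools will be stratified into the urban area group (6 schools", with the other four in the ger or mixed group. That makes 3 v 3 and 2 v 2 schools.

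The section on the primary outcome analysis fits a linear mixed model with school and individual as the only random effects and Satterthwaite degrees of freedom. It tests the before-after contrast between arms in each site at two-sided 0.025.

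**The concern.** In a before-after comparison of randomised schools, precision is limited by how differently schools change for reasons unrelated to the intervention, such as teachers, exam preparation or local events. A school intercept that is constant over time does not capture this, because it cancels from each school's change. If neither the simulation nor the analysis model lets schools change differently, the calculation treats every child as independent evidence about the intervention. With six and four schools that matters a great deal.

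Two things are at stake. A null result would be read as coming from a well-powered trial. A positive result would be read as controlled at 5% when the true error rate could be several times that.

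**Working it through.** **Inputs.** From the article: effect 0.2 SD; correlation r = 0.4, 0.5, 0.6; two-sided alpha 0.025 per site (critical value 2.241); 2337 children less 5% = 2220; 6 and 4 schools. Children per site are not stated, so they are back-solved. School-by-time variance is not stated, so it is an assumed range.

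**1. Reproduce Table 1 with no school-level variation in change.** Total variance at each time point is set to 1, so a child's change has variance 2(1 − r). With n children per arm:

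variance of the contrast = 2(1 − r) × 2/n; power = Φ(0.2/SE − 2.241)

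Solving for n from each stated power:

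| r | Urban n per arm | Ger or mixed n per arm |
|---|---|---|
| 0.4 | 682 | 407 |
| 0.5 | 665 | 398 |
| 0.6 | 666 | 393 |

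The implied n barely moves with r, as it should if the design effect is 1. Putting one n per site back in (668 and 400):

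| r | Urban: formula / stated | Ger or mixed: formula / stated | Disjunctive: formula / stated |
|---|---|---|---|
| 0.4 | 0.863 / 0.871 | 0.633 / 0.642 | 0.950 / 0.957 |
| 0.5 | 0.921 / 0.920 | 0.721 / 0.719 | 0.978 / 0.977 |
| 0.6 | 0.967 / 0.967 | 0.821 / 0.814 | 0.994 / 0.992 |

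Disjunctive power is 1 − (1 − urban)(1 − ger or mixed).

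**2. Check the total.** 2 × (668 + 400) = 2136, against 2220 available. Row by row, the implied totals are 2179, 2126 and 2117. The spare children allow a design effect of 2220/2179 = 1.02 to 2220/2117 = 1.05. At about 222 children per school, that is a between-school share of the variance of change of at most about 0.0002. With no dropout it is at most about 0.0004.

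**3. Let schools change differently.** Let t be the school-by-time variance at each time point and k the schools per arm (3 or 2). Then

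variance of the contrast = 2(1 − r) × 2/n + 2t × 2/k

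At r = 0.5 the variance of change is 1, so t = 0.25% of total variance is 0.5% of the variance of change. For t = 0.0025:

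- Urban: 2/668 + 0.01/3 = 0.00299 + 0.00333 = 0.00633, SE 0.0795. Power = Φ(2.514 − 2.241) = 0.608.
- Ger or mixed: 2/400 + 0.01/2 = 0.0100, SE 0.100. Power = Φ(2.000 − 2.241) = 0.405.

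| t (assumed) | Urban, normal critical value | Urban, 6 df (assumed) | Ger or mixed, normal critical value | Ger or mixed, 6 df (assumed) |
|---|---|---|---|---|
| 0.25% | 0.608 | 0.404 | 0.405 | 0.261 |
| 0.5% | 0.418 | 0.269 | 0.272 | 0.176 |
| 1% | 0.250 | 0.163 | 0.165 | 0.111 |
| Stated | 0.920 | | 0.719 | |

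The 6 df are ten schools less four site-by-arm cells, with a noncentral t distribution (critical value 2.969).

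**4. A much smaller variance.** Suppose the between-school share of the variance of change is only 0.001. The variance in step 1 is then multiplied by 1 + (m − 1) × 0.001, with m children per school. Site totals of 1340 and 798, practically the sizes above, give m of about 223 and 200 and multipliers of about 1.22 and 1.20. With normal critical values, urban power at r = 0.4/0.5/0.6 is 0.783/0.858/0.928 and ger or mixed power is 0.545/0.633/0.740. Urban no longer exceeds 0.8 in all settings, and ger or mixed no longer exceeds 0.8 at r = 0.6.

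**5. Type I error if the model omits the term.** Error = 2Φ(−2.241 × √(model variance / true variance)).

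- t = 0.25%: the variance ratios are 0.00633/0.00299 = 2.11 and 0.0100/0.0050 = 2.00. The error is about 0.12 urban and 0.11 ger or mixed, or 1 − 0.88 × 0.89 = 0.22 for either.
- t = 0.5%: the ratios are 3.23 and 3.00. The error is about 0.21 and 0.20, or 1 − 0.79 × 0.80 = 0.37 for either.

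**The case against.** **Clustering may have been simulated.** A reader might infer that the simulation ignored schools altogether. The article does not support that. School is a named level, a mixed procedure was used, and the cited method is not reproduced. A constant school intercept may well have been included. It would cancel from the before-after contrast and leave no trace in Table 1. An unprinted intraclass correlation in a condensed article is not in itself an error. What stands is narrower: whatever else was simulated, Table 1 leaves no room for material school-level variation in change.

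**The site sizes are fitted.** They are back-solved from the same table, so the match is a fit, not a derivation. A plain 6:4 split of the 2220 children (1332/888) overshoots the ger or mixed column by 4 to 5 points. The evidence is that one size per site fits three correlations and that the total nearly exhausts the available children.

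**Few degrees of freedom.** A reader might infer that power falls short even without school-by-time variation, since 6 df alone would give 0.74 and 0.50 at correlation 0.5. That is not the planned test. With no such variation, the Satterthwaite contrast keeps degrees of freedom near the number of children, and Table 1 applies.

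**Site-specific tests.** A reader might infer that testing each site contradicts the objective, "The primary objective of our study is to investigate the effectiveness of exercise intervention on academic achievement among children using a large cluster RCT", or the later listing, "The first subgroup analysis will focus on the location of the schools (urban and non-urban areas". But the per-site approach is consistent across the sample size, the stratified allocation and the primary analysis. The objective does not exclude it, and naming location again as a subgroup is a minor labelling matter.

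**Conclusion.** The point holds in this form. Table 1 follows from 2337 children only with a design effect on change of at most about 1.05, and the primary model builds in the same assumption. The simulated per-site alpha of 0.023 to 0.027 is what one would see when data and analysis share it, so it gives no assurance for schools that change differently.

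The three statements at issue are urban power above 0.8 throughout, both sites above 0.8 at correlation 0.6, and disjunctive alpha near 0.05. None is a property of the 3 v 3 and 2 v 2 design once such variation exists. The two power statements already fail when 0.1% of the variance of change lies between schools.

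The size of the loss rests on the assumed variance range and on the degrees of freedom. The revised powers are therefore an illustration, not an estimate of the trial's true power.

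**What to change.** 1. In the primary outcome analysis, add a school-by-time random effect with school-level degrees of freedom, or replace the model by a school-level analysis of change. State how the degrees of freedom are obtained.
2. Re-run the existing simulation with that model as the analysis, generating data over a stated range of school-by-time variance. Re-running it under the present model would only display the inflated alpha.
3. Restate Table 1 and the sentences that rest on it, and say which school-level variances were assumed.

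The cost is a less favourable power statement and wider confidence intervals. No extra schools or children are needed. A primary test pooled over the ten schools and stratified by site is an option for the sponsor to weigh, because it uses all the schools in one comparison. It would take primary status from the site-specific effects, and it is not needed to correct the error.

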### Allocation

We will perform stratified block randomization to allocate ten schools into the intervention and control arms. These schools will be stratified into the urban area group (6 schools) and the *ger* or mixed residential area group (4 schools) according to the location of the school. To ensure a balance between the two study arms, we will order the schools by the number of fourth grade students to form blocks for randomization in each residential group. Within the blocks, the schools will be randomly allocated to the intervention or control arm. To allocate the schools, arbitrary numbers given by the representative of each school will be used. The arbitrary numbers will be processed by a program on R statistical software, version 3.4.3 (The R foundation for statistical computing platform) which is developed by a researcher. Each school will be randomly allocated to intervention or control group based on the output of the R program.

The allocation will be conducted and announced to the representative of each school at a kickoff meeting.

### Blinding

According to the nature of the intervention, the participants and outcome raters, participants’ parents or guardians answering the questionnaires, and researchers taking the anthropometric and physical fitness function measurements will not be blinded to the allocation. However, the chief data analyst will be blinded to the allocation.

All data collected in this study will be entered in duplicate and managed using Microsoft Excel. The data file will be secured with a password, and access to information will be limited to designated members such as the researchers and RA. Paper-based documents such as consent forms, questionnaire response sheets, and forms for recording the physical fitness function and anthropometric measurements will be stored at a research institute in Ulaanbaatar. The data from the Flanker test will be stored on tablets and the internet server.

### Statistical methods

#### Analysis of the primary outcome

The baseline data of the intervention and control groups will be compared. The chi-squared test will be used for binary variables and the t-test will be used for continuous variables. To avoid overestimating the impact of the intervention, an intention-to-treat approach will be adopted to evaluate the impact on the primary and secondary outcomes. In this study, an individual’s data will be analyzed in the originally allocated arm even if the individual moves to a school in another area during study period.

To examine the effect of the intervention while taking the hierarchical structure into consideration, we will use a linear mixed effect model. In this model, the fixed effects are the group (intervention/control), site (Urban/ *ger* or mixed residential), and measurement time point with the following two interaction terms: the interaction between group and measurement time point, and the interaction between the group, measurement time point, and site. The random effects are school and individual. The degrees of freedom will be estimated using Satterthwaite approximation. For the primary analysis, we will compare the participants’ performance on the national year-end examination before and after the intervention using least squares means estimated by the interaction term of the group, measurement time point, and site. The Bonferroni method will be used as a multiplicity adjustment method. A significance level of 0.025 will be set for a two-sided test, and the 95% confidence interval will be calculated.

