## Methods/design

This study will be a collaborative effort by the National Center for Child Health and Development, Mongolian National Institute of Physical Education (MNIPE), and the University of Tsukuba. This study is a cluster-RCT using school as a cluster. A pilot study has already been done to confirm the feasibility and logistics of the planned intervention program and the assessment of the subjects’ physical fitness and cognitive function at one school in the study area.

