#### Analysis of secondary outcomes

In the secondary analysis, the same analytical method will be used as in the primary analysis for each test score (mathematics and language) and the continuous outcomes of BMI, sleeping hours, 20m shuttle run, each element of the Flanker test, side-to-side movement, and each SDQ score for mental health. We will use mixed-effects logistic regression for binary data. The covariate of this model is also the same as in the primary analysis. Although the frequency of exercise and playing outside hours constitute ordered data, they will be converted into binary data using a cutoff in the secondary analysis. The cutoff of the frequency of exercise will be between “1–2 days” and “3–4 days”, playing outside hours will be between “30 min-59 min” and “60 min-119 min”. Since the analysis of the secondary outcome is the exploratory evaluation, we will not adjust for the multiplicity of statistical testing.

In the analysis of cognitive function using the Flanker test, participants who fail to reach a correct rate of 50% will be excluded on the assumption that they do not understand the test.

In this study, any imputation will not be performed to missing data due to lost participants or imperfect data collection. The data will be analyzed using STATA V.13.1 (STATA/IC 13.1 for Mac, STATA Corp, [name] College Station, Texas), SAS Software 9.4 (SAS Inc., Cary, NC, USA), and SPSS statistics V.19.0 (IBM SPSS Statistics for Windows, IBM Corp, Armonk, New York).

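### The primary mixed model leaves out between-school variation in change, so its stated type I error and Table 1 power hold only if that variation is zero

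*Protocol article*

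**What the plan says.** The school is the unit of randomisation: "This study is a cluster-RCT using school as a cluster" (Methods/design). The Allocation section splits the ten schools into an urban stratum of six and a ger or mixed residential stratum of four, and randomises within blocks ordered by school size.

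Under Analysis of the primary outcome, the fixed effects are group, site and time point, plus the group-by-time and group-by-time-by-site interactions. The sentences that fix the error structure are: "The random effects are school and individual. The degrees of freedom will be estimated using Satterthwaite approximation". The primary test compares examination scores before and after the intervention, by group within site, using least squares means from the three-way interaction, at a two-sided level of 0.025. The protocol introduces this model as the way in which it accounts for the hierarchy.

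Under Analysis of secondary outcomes, "the same analytical method will be used as in the primary analysis for each test score (mathematics and language") and for the continuous outcomes; binary outcomes get a mixed-effects logistic model with the same covariates.

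The Sample size section reports a simulation and concludes: "In all assumption settings, the disjunctive alpha error is kept nearly equal to 0.05". The only correlation that it varies is the "correlation between measurement time points for the same individual, we assumed values of 0.4, 0.5 or 0.6". No school-by-time variance, and no intraclass correlation of change, appears anywhere.

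**The concern.** When schools are randomised, chance differences between schools in how they change are the error against which an effect on change must be judged. Between the May 2017 examination and the 2018 examination, teachers, examination preparation, marking or local events may differ from school to school. With 3 v 3 urban and 2 v 2 ger/mixed schools, a few such differences need not balance out.

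A school intercept does not absorb them. It is the same at both time points and is subtracted out of the contrast. The Satterthwaite method cannot help, because it approximates degrees of freedom only for variance components that are in the model. If schools do change differently, the standard errors of the primary result and of the secondary linear results are too small, and ordinary school-level drift can be declared an effect of exercise.

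**Working it through.** **Inputs from the protocol.** "2337 children are enrolled in the ten schools that participate in this study". "We assumed the standardized difference of the primary outcome to be equal to 0.2, and the dropout rate to be equal to 5" per cent. Within-child correlation rho is 0.4, 0.5 or 0.6. The level is 0.025 two-sided per site, so z = 2.2414. There are 6 + 4 schools, taken as k = 3 per arm (urban) and k = 2 per arm (ger/mixed).

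**Inputs not in the protocol.** The site split of children is not stated, so children per arm were back-calculated from Table 1: about 668 urban and 400 ger/mixed. The school-by-time variance s2, as a share of total variance, is not given, so a range is shown.

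**Step 1: variance of the contrast in the planned model.** School and child intercepts cancel. With n children per arm and unit total variance, V0 = 2 x 2(1 - rho)/n = 4(1 - rho)/n. No school term remains.

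**Step 2: reproduce Table 1.** Power is Phi(0.2/sqrt(V0) - 2.2414), and the total is 1 - (1 - Pu)(1 - Pg). Example, urban at rho 0.5: V0 = 2/668 = 0.00299, 0.2/sqrt(V0) = 3.655, power = Phi(1.414) = 0.921.

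| rho | Computed total / urban / ger-mixed | Table 1 |
|---|---|---|
| 0.4 | 0.950 / 0.863 / 0.633 | 0.957 / 0.871 / 0.642 |
| 0.5 | 0.978 / 0.921 / 0.721 | 0.977 / 0.920 / 0.719 |
| 0.6 | 0.994 / 0.967 / 0.821 | 0.992 / 0.967 / 0.814 |

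All nine agree within 0.01. Because the two n were fitted, a check on the total matters more. Solved separately at each rho, Table 1 implies 2117 to 2179 children in all, against 2337 x 0.95 = 2220 expected completers. The stated power thus contains almost no school design effect.

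**Step 3: type I error when schools change differently.** The true variance is V1 = V0 + (2/k) x 2 x s2 = V0 + 4 s2/k, while the test still uses V0. The error is 2[1 - Phi(2.2414 x sqrt(V0/V1))]. Example, urban, s2 = 0.005, rho 0.5: V1 = 0.00299 + 0.00667 = 0.00966; sqrt(V0/V1) = 0.557; 2.2414 x 0.557 = 1.248; error = 0.21. For ger/mixed: V0 = 0.005, V1 = 0.015, ratio 0.577, product 1.294, error = 0.20.

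| s2 (share of total variance) | Urban | Ger/mixed | At least one site |
|---|---|---|---|
| 0% | 0.025 | 0.025 | 0.05 |
| 0.1% | 0.06 | 0.06 | 0.12 |
| 0.25% | 0.12 | 0.11 | 0.22 |
| 0.5% | 0.21 | 0.20 | 0.37 |
| 1% | 0.34 | 0.32 | 0.55 |

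REML fits of the planned model to simulated data, with unequal school sizes and 5% dropout (600 runs per value, rho 0.5), gave urban / ger-mixed / overall 0.063 / 0.063 / 0.123 at 0.1%, 0.213 / 0.212 / 0.380 at 0.5% and 0.373 / 0.338 / 0.578 at 1%.

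**Step 4: power of a test at school level.** Take ten equal schools of 222 completers (2220/10). The variance is (2/k)[2(1 - rho)/222 + 2 s2]. The degrees of freedom are 10 schools - 4 group-by-site cells = 6, which raises the critical value from 2.24 to 2.97. Example, urban, rho 0.5, s2 = 0: variance = (2/3)(1/222) = 0.0030, standard error 0.055, noncentrality 0.2/0.0548 = 3.65, power 0.73. Over rho 0.4-0.6:

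| s2 | Urban | Ger/mixed |
|---|---|---|
| 0% | 0.65-0.83 | 0.47-0.65 |
| 0.5% | 0.26-0.29 | 0.17-0.20 |
| 1% | 0.16-0.17 | 0.11-0.12 |

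Type I error in these simulations was 0.024-0.026 per site at every s2 tried.

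**The case against.** **The inflation is conditional.** At exactly zero school-by-time variance the planned test has its nominal error, and the protocol gives no value. This stands. A reader might infer that the error is far above the stated level as a matter of fact; the documents do not establish that. They show only that nothing in the model guards against it, and that the inflation rises steeply once the variance leaves zero.

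**School is in the model.** This also stands. A reader might say that the analysis ignores the school altogether. It does not: school is a named random effect, and what is missing is school variation in change. The word intercept is not the protocol's own, and an article may leave covariance details to a fuller plan. But the article does state the random effects, and Table 1 fits the intercept reading.

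**Table 1 already shows alpha near 0.05.** This does not rebut the point. The alpha columns are what the planned model returns when school-by-time variance is zero, and the simulation is not described as including any.

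**Identity with a t-test on changes.** This holds exactly only for complete data. Because a mixed model keeps children with one score, a check at 5% missing follow-up gave standard errors of 0.0560 and 0.0562, a negligible gap.

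**Secondary outcomes.** The protocol calls these analyses exploratory. The logistic models lack the same term, but cancellation is not exact there, and no inflation was demonstrated for them.

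**Conclusion.** The concern holds in conditional form. The primary contrast is tested against within-child variance, with degrees of freedom near the number of children, although schools were randomised. The stated 0.025 per site, 0.05 overall and Table 1 power require zero school-by-time variance, a condition that the protocol neither states nor supports. At rho 0.5, 0.1% of total variance already more than doubles the per-site error (to about 0.06), and 0.5% takes it to 0.20-0.21, with 0.37 overall.

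This rests on three things: the random-intercept reading, child numbers back-calculated from Table 1, and assumed values of s2. The size is open; the dependence on zero is not. The primary p-values and confidence intervals turn on it, so it should be settled before analysis. The demonstration covers linear outcomes only.

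**What to change.** Add a school-by-time random effect to the primary model and to the secondary linear models, or analyse school mean changes in two stages. Use small-sample degrees of freedom at school level: 6 when residual variation is pooled over sites. State that the term stays if it is estimated at zero, by allowing a negative estimate or by using the two-stage analysis; dropping it would restore the child-level test. For the logistic models, say how school variation in change will be handled. Restate the alpha and power of Table 1 under the revised model with a declared school-by-time variance and a range around it.

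Two apparent alternatives need care.

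- **Baseline adjustment.** A model of the 2018 score adjusted for the 2017 score with a school intercept is not equivalent, because part of the stable school difference remains in the contrast. In a simulation of 3 v 3 schools of 222 at rho 0.5, zero school-by-time variance and an assumed school intraclass correlation of 0.05, its effect estimate had an SD of 0.109, about twice the 0.055 of the change contrast.
- **Permutation within a site.** This cannot support a result at 0.025. There are at most 20 urban and 6 ger/mixed allocations, so the smallest two-sided p is 2/20 = 0.10 and 2/6 = 0.33. If the blocks are pairs (block size is not stated), there are 8 and 4 allocations, giving 0.25 and 0.50.

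The wording and code change is short. The real cost is wider intervals and the lower power shown above, which should be disclosed. With site-specific degrees of freedom (4 and 2) instead of the pooled 6, power at zero school-by-time variance falls further, to 0.52-0.70 urban and 0.19-0.26 ger/mixed.
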